### Elimination From the Trial

Patients will be omitted from the trial if the situation changes to incompatible with the trial protocol. This can happen because of the following reasons: a neoplastic condition is found at the time of management; the general status of the patient worsens owing to other health issues not related to cholelithiasis (eg, myocardial infarction) and the patient needs urgent interventions not included in the trial protocol; and LC is converted to open cholecystectomy before IOC in the “cholecystectomy first” arm. Additionally, if the patient refuses to further participate in the trial, all the patient’s data are eliminated and further follow-up is not carried out. Informed consent will be obtained from all study participants.

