### Blinding

As both management strategies (endoscopic evaluation and intraoperative examination) differ in nature and postprocedure effect on the patient, complete blinding of participants is not possible. Before enrollment in the trial, the participant, treating clinician, and investigator will not know to which group the participant is assigned.

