### Follow-Up

Participants are followed as treated inpatients after LC (short-term surveillance) and for 6 months after hospitalization (long-term surveillance). In the short-term surveillance period, postprocedural adverse events, signs of cholestasis, and need for repeated procedures are recorded. In the long-term surveillance period, participants are encouraged to contact the investigators if any symptoms of recurrent cholelithiasis are suspected. Participants will be contacted via phone or email 6 to 12 months later. Their health status will be evaluated using a questionnaire on the possible symptoms of choledocholithiasis (Multimedia Appendix 1). If any symptoms of possible gallstone disease are observed, the participant is invited for additional investigation (biochemical blood tests, transabdominal ultrasound, and MRCP on demand). All the enrollment, intervention, and surveillance procedures are listed in Multimedia Appendix 2.

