### Statistical Analysis

The sample size was calculated in reference to collected data on the management of choledocholithiasis in the trial center Vilnius University Hospital Santaros Klinikos [11]. In our previous study, the mean treatment durations for different management strategy groups (LC-IOC first and ERCP first) were 5.37 and 7.13 days, with SDs of 2.5 and 2.8, respectively, and these findings were used to calculate the requested sample size. The program G*Power version 3.1.9.2 was used for calculations. It was calculated for a two-tailed *t* test for means of two independent groups. The significance level was selected to be .05, with a power of 0.8. The required sample size is 74 (37 valid participants in each of the two groups).

The endpoints in different management groups will be analyzed using the chi-square test or *t* test for independent means. Two-sided hypotheses are to be checked, and a *P* value <.05 will be considered statistically significant. If the distribution is nonnormal, a transformation, such as the logarithm or square root function, can be applied to obtain a normal distribution or nonparametric tests, such as the Mann-Whitney test, can be used. To evaluate the achieved power, a post-hoc power analysis calculation will be performed.
As for the primary outcome, a difference of 2 days of hospital stay will be considered clinically meaningful.

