### Outcomes

The primary endpoint is the length of hospital stay (duration from enrollment into the trial to discharge, in days).

The secondary endpoints are as follows:

1. Diagnostic accuracy of the different management strategies (proportion of correctly diagnosed [true positive and true negative] cases in the entire sample; time frame: 6 to 12 months).

2. Technical success of diagnostic and therapeutic biliary procedures (IOC, EUS, ERCP) (during the active treatment period). For IOC, successful cannulation and contrast media injection into the CBD are considered. For EUS, successful visualization of the CBD is considered. For ERCP, successful cannulation and contrast media injection into the CBD are considered. Successful CBD clearance is also considered.

3. Postoperative course and possible complications of treatment (time frame: up to 1 month). With regard to adverse events of endoscopic interventions and IOC, we consider (1) bleeding, hematemesis and/or melena, or hemoglobin drop >20 g/L; (2) perforation, evidence of air or luminal contents outside the gastrointestinal tract; (3) post-ERCP pancreatitis, new or worsening abdominal pain persisting for at least 24 h and requiring analgesics after ERCP in conjunction with an elevation in serum amylase or lipase levels greater than three times the normal upper limit [16,17]. We also consider assessment of the postoperative course by the Clavien-Dindo classification of surgical complications [18].

4. Cost of treatment (charges for diagnostic procedures, invasive procedures, surgery, and antibacterial treatment, if needed, as well as hospital charges).

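### Refusing further participation erases all of a patient's data, including a length of stay and complications already fully observed

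*Protocol article*

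**What the plan says.** Under Elimination From the Trial, the protocol article gives a separate rule for refusal: "if the patient refuses to further participate in the trial, all the patient’s data are eliminated and further follow-up is not carried out". This has two consequences, erasure of what exists and an end to follow-up. The trigger is refusal to continue, whenever it occurs; a request for erasure is not required.

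The timing of the outcomes is set elsewhere:

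- Outcomes: "The primary endpoint is the length of hospital stay (duration from enrollment into the trial to discharge, in days".
- Outcomes, third secondary endpoint: "Postoperative course and possible complications of treatment (time frame: up to 1 month".
- Follow-Up, inpatient phase: "In the short-term surveillance period, postprocedural adverse events, signs of cholestasis, and need for repeated procedures are recorded".
- Follow-Up, later phase: surveillance continues "for 6 months after hospitalization (long-term surveillance", and "Participants will be contacted via phone or email 6 to 12 months later".

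Under Blinding, the article accepts that "complete blinding of participants is not possible". No section of the article keeps data gathered before a refusal.

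**The concern.** Stopping follow-up when a patient refuses is unavoidable. Deleting what has already been observed goes further. For months after discharge, a withdrawal removes a length of stay with nothing missing from it, together with any complication recorded in hospital.

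Two things are at stake. First, the primary and safety comparisons would be made only in patients who stayed in the trial to the end, a group defined after randomisation. In an open trial, a patient's decision to leave can reflect the arm or a difficult course, so the groups compared may no longer be those that randomisation made alike. Second, procedure-related harms are likely to be few, so the loss of even one or two records could alter the safety picture. A statistical analysis plan cannot repair this later, because erased data cannot be analysed.

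**Working it through.** **1. Timing of outcomes against the period in which refusal can occur**

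| Item | Complete by | Section |
|---|---|---|
| Length of stay (primary) | discharge | Outcomes |
| Technical success of biliary procedures | end of active treatment | Outcomes |
| Complications | 1 month | Outcomes |
| Diagnostic accuracy | 6 to 12 months | Outcomes |
| End of participation | contact at 6 to 12 months | Follow-Up |

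For a patient who withdraws between month 1 and the late contact, only the accuracy endpoint is incomplete. The rule nevertheless removes every row.

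**2. The plan's own sample size, and whether power is the problem**

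Inputs (Statistical Analysis): the planning means "were 5.37 and 7.13 days, with SDs of 2.5 and 2.8, respectively"; two-sided alpha 0.05; power 0.8.

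- Difference: 7.13 − 5.37 = 1.76 days.
- Pooled SD: √((2.5² + 2.8²)/2) = 2.654.
- Standardised difference: 1.76/2.654 = 0.663.
- Noncentral t power: 0.792 with 36 per arm and 0.803 with 37 per arm. The stated 37 per arm (74 in total) is reproduced.

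Planned enrolment is 106 (Abstract), or 53 per arm at 1:1. Since 74/0.70 = 105.7, this leaves room for about 30% loss, although the article does not give that as the reason. Power is 0.922 with 53 per arm, 0.889 with 47, 0.852 with 42 and 0.803 with 37. Loss of numbers is therefore well covered, and what remains is possible bias.

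**3. Illustrations of bias (withdrawal patterns assumed, not taken from the documents)**

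*Simple shift.* Suppose 5 of 53 patients in one arm withdraw and their stays were x days longer than those of the other 48. The arm mean is then understated by (5/53) × x.

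- x = 2: 0.19 days; x = 4: 0.38 days.
- Relative to the 1.76-day planning difference: 11% to 21%.
- Relative to the 2-day clinically meaningful difference: 0.19/2 = 9% to 0.38/2 = 19%.

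*Milder selection.* If 20% of the patients in the longest-stay quarter of one arm withdraw (5% of that arm), its mean shifts by about −0.19 days (simulated, gamma-distributed stays with mean 6.25 and SD 2.65).

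*Extreme selection.* Here the withdrawals are exactly the longest stays in one arm (gamma-distributed stays, 53 per arm, 20,000 runs). The null column uses a common mean of 6.25 and SD of 2.65.

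| Erased | Expected difference if erased from 'endoscopy first' | Expected difference if erased from 'cholecystectomy first' | Two-sided type I error with no true difference |
|---|---|---|---|
| 1 | 1.60 | 1.89 | 0.06 |
| 2 | 1.48 | 2.01 | 0.09 |
| 3 | 1.38 | 2.12 | 0.13 |
| 5 | 1.18 | 2.29 | 0.23 |

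The expected difference moves down or up from 1.76 according to which arm loses patients.

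*Safety counts.* The Introduction gives a 5% to 10% complication risk for ERCP and a 25% to 75% stone probability for the intermediate-risk group. Taking the stone probability as the share who undergo ERCP is an assumption. Expected ERCP complications per arm are then 53 × 0.25 × 0.05 = 0.7 to 53 × 0.75 × 0.10 = 4.0, and 53 × 0.50 × 0.075 = 2.0 at the midpoints. At the midpoints, erasing one affected patient removes about half of an arm's count.

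**The case against.** The strongest reply is that the rule itself does not create bias. It becomes harmful only if withdrawal is related to outcome or arm, and no section says that it is. Unrelated withdrawal would cost precision, which the surplus of 106 over 74 absorbs. This stands as a limit on what can be claimed. It does not justify deleting complete outcomes, and a larger sample does not remove bias where withdrawal is related to outcome.

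Four stronger readings are tempting, and the documents do not support them.

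- *Declining the late call or an extra test triggers erasure.* The trigger is refusal to take part in the trial. Follow-Up describes contact and an invitation to further investigation; it does not equate declining these with withdrawal.
- *'Endoscopy first' is uniquely exposed because cholecystectomy is still to come.* Under Procedure, patients in 'cholecystectomy first' with a positive cholangiogram also usually face a further procedure, postoperative ERCP. Cholecystectomy was already indicated for everyone. No direction of imbalance follows. If long stays were lost mainly from 'endoscopy first', the effect would work against the hypothesised advantage of 'cholecystectomy first'.
- *Erased patients leave no trace.* Envelopes are numbered and that number is the patient's trial number (Randomization and Data Protection), so an erasure should show as a gap in the sequence. What is lost is the outcome; the fact that a patient was enrolled can still be seen.
- *The bias has a known size.* The number of withdrawals and their excess stay have no source in the documents.

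A consent or legal duty might require erasure. The article cites none for this rule, and the consent pages are not available, so the point cannot be settled here.

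**Conclusion.** The point holds as a defect in the data-retention rule. As written, a withdrawal at any time eliminates everything, including a length of stay complete since discharge and complications already recorded. That conclusion rests on the text alone.

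Bias is a foreseeable risk in an open trial; the documents do not establish it. A reader might infer that data are lost selectively by outcome, or that randomisation no longer protects the comparisons. Neither follows without knowing how many patients withdraw, from which arm and why. The 0.19 to 0.38 days, the type I error figures and the complication counts all depend on assumed inputs and show only what a handful of withdrawals could do. The rule should be amended, because it discards usable primary and safety data and leaves open a route to bias that is easily closed.

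**What to change.** Replace the refusal rule with text along these lines:

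> If a participant withdraws, trial contact and further data collection stop. Data collected up to that date (enrolment and discharge dates, procedures, adverse events) are kept and analysed in the randomised arm, as far as consent and law allow. Data are erased only on the participant's explicit request. Withdrawals and erasures are reported by arm and time point.

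Record declining a single procedure, call or investigation separately from withdrawing from the trial, and both separately from refusing use of data.

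The cost is a protocol amendment and revised consent wording for new participants, with no extra patients or procedures. With 66 of 106 enrolled by June 2020, the new wording could cover at most 106 − 66 = 40 participants at that date. For those already enrolled, the wording they signed must be respected, so some erasures may be irreversible. Those can still be counted and reported by arm.

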### Randomization and Data Protection

Eligible patients who provide informed consent will be assigned to the groups “endoscopy first” or “cholecystectomy first” randomly, according to a premade sequence. The sequence is generated by a randomization website [15]. The sequence is created using block randomization of two elements A and B (“endoscopy first” and “cholecystectomy first”) in a ratio of 1:1. According to the sequence, sheets with group names are enclosed in opaque envelopes. Envelopes are numbered, and the envelope number is the patient number in the trial. When a new participant is enrolled, the topmost envelope is opened by one of the investigators and the participant is randomized into the specified group.

All collected data are coded, that is, every case receives an individual number. Only coded data will be employed for statistical analysis and publishing. Uncoded data are available only for researchers of the trial and, on special and reasonable request, for the coordination center for biomedical research of the institution and Biomedical Research Ethics Committee.

Data are processed and stored in an electronic database, and physical (“paper”) copies are stored at the trial center in accordance with procedures established by law.

### Procedure

The participants of the trial will undergo CBD evaluation depending on the group assignment. For the group “endoscopy first,” EUS is used to evaluate bile ducts. If stones are seen in the extrahepatic bile ducts, ERCP and CBD stone removal are performed during the same general endotracheal anesthesia. LC is performed after endoscopic procedures as soon as possible. In the group “cholecystectomy first,” LC with IOC is performed. If stones are found, postoperative ERCP with CBD stone removal is applied (during cholecystectomy if the CBD is completely blocked or as soon as possible).

EUS is performed with linear or radial Olympus ultrasound endoscopes. The CBD, pancreatic head, and adjacent structures are visualized from the duodenal bulb and descending duodenum. EUS is considered positive for a CBD stone when a constant hyperechogenic lesion with acoustic shadowing is seen in CBD projection.

ERCP procedures are performed by experienced endoscopists (each has more than 5 years of experience in ERCP and has done more than 500 procedures). Olympus side-viewing endoscopes (TJF-160VR) are used. Primary deep selective cannulation of the CBD is performed with a sphincterotome or cannula and guidewire technique. Diatrizoate (Urografin, Bayer) and iohexol (Omnipaque, GE Healthcare) are used as contrast media. Endoscopic sphincterotomy is performed over a guidewire technique with an Olympus pull-type sphincterotome. Papillary balloon dilation using a through-the-scope balloon catheter is applied when a stricture is indicated. Stones are removed using a retrieval balloon catheter and/or a Dormia basket. Complete clearance of the CBD is documented with a balloon catheter cholangiogram at the end of the procedure. ERCP is considered positive when a filling defect is seen in the cholangiogram and/or a stone is evacuated from the CBD. ERCP is considered unsuccessful when cannulation of bile ducts is technically impossible.

All patients will undergo a standard four-port LC (a 10-mm port at the umbilicus, a 10-mm port at the subxyphoid, a 5-mm port at the bottom of the gallbladder, and a 5-mm port at the right epigastrium). A 30-degree laparoscope is used for intra-abdominal visualization. After exposure and identification of the elements of the hepatocystic triangle, a small transverse cut is made in the cystic duct close to the gallbladder infundibulum with laparoscopic scissors. A 4-French cholangiogram catheter is placed in a 5-mm cholangiography fixation clamp and then inserted into the cystic duct. After verifying the absence of leakage at the catheter insertion site, contrast medium (Urografin) diluted in NaCl 0.9% solution (1:1 ratio) in a 20-mL syringe is injected under fluoroscopic vision (C-arm, Siemens GmbH). Cholangiograms are assessed by the operating surgeon and radiologist. IOC is considered positive when there is a filling defect or lack of contrast evacuation to the duodenum.

### Blinding

As both management strategies (endoscopic evaluation and intraoperative examination) differ in nature and postprocedure effect on the patient, complete blinding of participants is not possible. Before enrollment in the trial, the participant, treating clinician, and investigator will not know to which group the participant is assigned.

### Follow-Up

Participants are followed as treated inpatients after LC (short-term surveillance) and for 6 months after hospitalization (long-term surveillance). In the short-term surveillance period, postprocedural adverse events, signs of cholestasis, and need for repeated procedures are recorded. In the long-term surveillance period, participants are encouraged to contact the investigators if any symptoms of recurrent cholelithiasis are suspected. Participants will be contacted via phone or email 6 to 12 months later. Their health status will be evaluated using a questionnaire on the possible symptoms of choledocholithiasis (Multimedia Appendix 1). If any symptoms of possible gallstone disease are observed, the participant is invited for additional investigation (biochemical blood tests, transabdominal ultrasound, and MRCP on demand). All the enrollment, intervention, and surveillance procedures are listed in Multimedia Appendix 2.

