At the Center of Abdominal Surgery of Vilnius University Hospital Santaros Klinikos, an original prognostic index (Vilnius University Hospital Index [VUHI]) is being used for the prediction of choledocholithiasis risk before laparoscopic cholecystectomy (LC). Recently, we evaluated its accuracy and determined new threshold values for low, intermediate, and high risk groups [11]. The intermediate risk group (risk for choledocholithiasis of 25%-75%) would benefit from additional examination before ERCP. EUS and IOC are less invasive procedures with high accuracy for identifying CBD stones. These procedures will be applied for patients with intermediate risk of CBD stones and will help to decide if ERCP is indicated.

We aim to compare EUS as the first diagnostic biliary intervention to LC with IOC in patients with intermediate risk of choledocholithiasis in order to evaluate the accuracy, technical success, and safety of these two management strategies.

The hypothesis is that LC with IOC (“cholecystectomy first” strategy) will decrease both the length of hospital stay and morbidity by lessening the number of endoscopic investigations (EUS and ERCP) and thus the number of possible complications of ERCP, as well as decreasing the complications related to delayed cholecystectomy.

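### The complication endpoint is given a window of up to 1 month, but the article describes adverse-event recording only for the inpatient period after cholecystectomy

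*Protocol article*

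**What the plan says.** All references are to the protocol article.

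- **Outcomes, secondary endpoint 3** sets the window: "Postoperative course and possible complications of treatment (time frame: up to 1 month". It names bleeding, perforation and post-ERCP pancreatitis as adverse events of the endoscopic interventions and intraoperative cholangiography (IOC), and grades the postoperative course by Clavien-Dindo.
- **Follow-Up** defines two periods: "Participants are followed as treated inpatients after LC (short-term surveillance) and for 6 months after hospitalization (long-term surveillance".
- **Follow-Up** assigns adverse events to the first of these: "In the short-term surveillance period, postprocedural adverse events, signs of cholestasis, and need for repeated procedures are recorded".
- **Follow-Up** gives the second period a different content. Between discharge and the late contact, "participants are encouraged to contact the investigators if any symptoms of recurrent cholelithiasis are suspected". Then, "Participants will be contacted via phone or email 6 to 12 months later", and "Their health status will be evaluated using a questionnaire on the possible symptoms of choledocholithiasis".
- **Follow-Up** also says that Multimedia Appendix 2 lists all surveillance procedures. That appendix is not shown.
- **Introduction** makes complications part of the hypothesis: the 'cholecystectomy first' strategy "will decrease both the length of hospital stay and morbidity".

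**The concern.** The window in Outcomes and the recording period in Follow-Up do not match. Nothing described would elicit bleeding, perforation, pancreatitis or a Clavien-Dindo event between discharge and 1 month. The late questionnaire asks about symptoms of bile duct stones, not about complications of the procedures.

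The start of the window is also unclear. Short-term surveillance begins after LC, but in 'endoscopy first' the endoscopic ultrasound (EUS) and any ERCP come before LC. Taken at its word, the text leaves out the complications that the endpoint most needs to count in that arm.

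Morbidity is half of the stated hypothesis. The Discussion says that if the difference in stay is not significant, the other outcomes remain for comparing the strategies. The Blinding section concedes that complete blinding is not possible. If a patient's observation ends at discharge, ascertainment of the safety endpoint is tied to discharge timing, and discharge also ends the primary endpoint, length of stay.

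**Working it through.** **1. The sections side by side**

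| Item | Outcomes | Follow-Up |
|---|---|---|
| Start of complication window | not stated | after LC |
| End of complication window | up to 1 month | end of inpatient period |
| Collection from discharge to 1 month | implied by the time frame | patient-initiated, for recurrent gallstone symptoms |
| First active contact after discharge | not stated | 6 to 12 months, stone-symptom questionnaire |

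The endpoint as defined is not the one that these procedures would produce.

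**2. Which arm would be observed less?**

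Length of stay runs from enrollment to discharge (Outcomes). Short-term surveillance runs from LC to discharge (Follow-Up). The Discussion attributes the longer two-stage stay to the wait between procedures, which in 'endoscopy first' falls before LC. A shorter total stay therefore does not imply a shorter window after LC. Two readings pull in opposite directions:

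- *Recording from any procedure to discharge.* In 'endoscopy first', ERCP is followed by the wait and the LC stay. In 'cholecystectomy first', ERCP is usually postoperative, and so nearer discharge. The pancreatitis definition needs pain lasting at least 24 h, so a patient discharged within a day of ERCP could not meet it as an inpatient. This would under-count in 'cholecystectomy first'.
- *Recording literally after LC.* Complications of EUS or ERCP before LC in 'endoscopy first' drop out. Patients with stones in 'cholecystectomy first' may also stay longer after LC while awaiting ERCP. This would under-count in 'endoscopy first'.

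**3. A purely illustrative size**

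Inputs from the article: earlier mean treatment durations of 5.37 days (LC-IOC first) and 7.13 days (ERCP first), from Statistical Analysis; 106 participants (Abstract) at 1:1, so 53 per arm. Assumed: the same true 30-day risk of 10% in both arms (5.3 true events each), observation equal to those mean durations, and event timing as below.

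Share recorded by day *t*:
- uniform timing: *t*/30
- exponential timing with mean *m*: (1 − exp(−*t*/*m*)) / (1 − exp(−30/*m*))

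Example for *m* = 3: (1 − exp(−5.37/3)) / (1 − exp(−10)) = 0.833, and with 7.13 days 0.907. Expected recorded events are 53 × 0.10 × 0.833 = 4.42 and 53 × 0.10 × 0.907 = 4.81.

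| Assumed timing | Share recorded, 5.37 v 7.13 days | Ratio | Expected events | Difference |
|---|---|---|---|---|
| Uniform over 30 days | 17.9% v 23.8% | 0.753 | 0.95 v 1.26 | 0.31 |
| Exponential, mean 10 days | 43.7% v 53.7% | 0.815 | 2.32 v 2.84 | 0.52 |
| Exponential, mean 7 days | 54.3% v 64.8% | 0.838 | 2.88 v 3.43 | 0.55 |
| Exponential, mean 3 days | 83.3% v 90.7% | 0.918 | 4.42 v 4.81 | 0.39 |

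At an assumed 5% risk the largest difference is 0.28 events (1.44 v 1.72). At 20% it is 1.11 (5.76 v 6.87).

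The overall loss is larger than the difference between arms. Of 10.6 true events at 10% risk, the recorded total would be 4.42 + 4.81 = 9.2 (mean 3 days), 2.32 + 2.84 = 5.2 (mean 10 days) or 0.95 + 1.26 = 2.2 (uniform).

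These figures do not estimate bias in this trial. The durations are total stays, not stays after LC, and the longer one comes from an ERCP-first group, not an EUS-first group. The clock starts with the stay and not with the procedure. The stay is held fixed, although a complication can itself delay discharge.

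**4. Sample size**

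The stated 74 reproduces: SD = √((2.5² + 2.8²)/2) = 2.654, effect size = 1.76/2.654 = 0.663, and the exact *t* test gives power 0.803 at 37 per group (0.792 at 36). It rests on length of stay and is not touched by this point.

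**The case against.** The strongest reply is that the article never says adverse events are recorded *only* until discharge. It is a condensed account, and it refers to Multimedia Appendix 2 for the full schedule, which could contain a 1-month contact or a record review. This stands as a limit on the point: the gap lies in what the article describes, not in what is known to be done. It does not remove the mismatch, because Follow-Up describes both surveillance periods and places adverse events in the inpatient one.

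A reader might infer more: that the arm discharged sooner is watched for less time and will therefore look safer, to the advantage of the hypothesised winner. The documents do not support this. Stay and surveillance start at different points, the two-stage wait precedes LC, and a literal start after LC would bias the other way.

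It can also be said that this is one secondary endpoint and that, on illustrative figures, the arms would differ by less than one event at 10% risk. That stands too. Any choice of fixed window also has a cost: counting 30 days from randomisation, for example, gives fewer days after LC to the arm operated on later. That is a reason to state the choice openly, not to leave it open.

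**Conclusion.** The point holds in a limited form. Outcomes and Follow-Up disagree on the period over which complications are counted. Followed as written, the procedures would give an inpatient, post-LC endpoint rather than a 1-month one. Ascertainment would be incomplete, would depend on when patients are discharged and on the order of procedures, and may differ between arms.

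Neither the direction nor the size of any bias is established. The between-arm difference is probably small: 0.3 to 0.6 expected events at an assumed 10% risk with 53 per arm, under assumed onset times and stays borrowed from an earlier comparison. Under-recording in both arms could matter more. All of this is subject to Multimedia Appendix 2. The matter should be corrected because morbidity is part of the hypothesis, but it affects a secondary endpoint only.

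**What to change.** Reconcile Outcomes and Follow-Up as follows.

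1. **State one fixed window with an explicit start that covers all trial procedures in both arms.** For example, it could run from randomisation, or from the first trial procedure, to 30 days after the last trial procedure. Note in the text that the choice of start and end shifts post-procedure days between arms.
2. **Record adverse events throughout that window**, including those before LC in 'endoscopy first'.
3. **Collect events after discharge in the same way in both arms**, through a hospital-record check and fixed questions on complications and readmission added to the contact already planned.
4. **If this is not done**, restate the time frame as until discharge and drop the 1-month claim.

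If Appendix 2 already contains a 1-month assessment, Follow-Up need only say so and give the start of the window.

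The cost is an amended endpoint line, a few questions and one record check per patient. With 66 of 106 patients enrolled by June 2020, it could be applied fully to the remaining 40. For those already enrolled, the record and the planned contact can be used, or the record alone where that contact has already taken place. The small downside is imperfect recall at 6 to 12 months, which the record check partly offsets. The sample size does not change.
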